There are several advantages if pulpotomy can be offered as a substitute to the standard pulpectomy treatment for the management of irreversible pulpitis in vital primary molars. The ribbon-like torturous root canal anatomy in primary molars makes pulpectomy a difficult procedure for general dentists to perform, often requiring a child in pain to be referred to a specialist paediatric dentist for definitive treatment. In many situations, specialist care may not be easily accessible, or parents may not be able to afford its costs. Consequently, some parents may opt to extract the painful primary molar tooth of their child, resulting in complications such as the loss of function and arch integrity. The technically simpler pulpotomy procedure is not only less challenging for general dentists but is also potentially less time-consuming and easier for young patients to tolerate, both very important advantages in the dental treatment of children. Moreover, the pulpotomized primary tooth retains the regenerative/repair potential of the remnant radicular pulp and the proprioceptive sensation of the tooth. Finally, treatment complications sometimes associated with pulpectomy (e.g., extrusion of root filling material beyond the primary root apex) can be avoided if pulpotomy is the treatment of choice.

There is limited research on whether pulpotomy can be offered as an alternate treatment to pulpectomy in vital primary molars diagnosed with irreversible pulpitis. A prospective cohort study of pulpotomy in 50 vital primary teeth with irreversible pulpitis reported 93% clinical success and 90% radiographic success after one year of treatment [29]. A more recent retrospective study found higher clinical success rates for pulpotomy (99%) than pulpectomy (88%) in primary molars with carious pulp exposures or symptomatic irreversible pulpitis over an 18-month period [30]. To the best of our knowledge, there have been no RCTs comparing treatment outcomes of pulpotomy vs. pulpectomy for management of irreversible pulpitis in vital primary molars. This study aims to fill this research gap and could be of great importance in initiating a paradigm shift in the treatment of vital primary molars diagnosed with irreversible pulpitis. The objectives and hypothesis of the study are detailed below.

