### Target sample size

Sample size determination for this binary outcome non-inferiority randomised trial was calculated using a computer-generated system available online (https://www.sealedenvelope.com/power/binary-noninferior/). Based on previous clinical studies [29–31], a 95% success rate was assumed for both treatment interventions along with a 17% non-inferiority margin. Even an overall success rate of 78% for the experimental pulpotomy intervention would be considered non-inferior to the standard pulpectomy intervention. To obtain a power of 80% (β = 0.20) and a 2-sided α equal to 0.05, approximately 42 patients for both groups will be needed. To compensate for loss during follow-up and other causes of attrition, the targeted sample size will be 50 vital primary molar teeth diagnosed with irreversible pulpitis, distributed equally between the two trial treatment arms.

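### The 95% success assumed in both arms is tied to no endpoint or time point, and the 80% power does not hold at the stated alpha or at the only radiographic rate reported

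*Protocol article*

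**What the plan says.** Target sample size (protocol article) states that "a 95% success rate was assumed for both treatment interventions", together with a non-inferiority margin of 17 points. The assumption is attributed to references 29 to 31. Power is set at 80% with "a 2-sided α equal to 0.05", from which "approximately 42 patients for both groups will be needed"; the target is then raised to 50 teeth to cover attrition. The same paragraph says that an overall success rate of 78% for pulpotomy would still count as non-inferior.

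Background/rationale describes two of the three sources:

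- Reference 29, a prospective cohort of pulpotomy in 50 teeth, "reported 93% clinical success and 90% radiographic success after one year of treatment".
- Reference 30, a retrospective comparison over 18 months, gives clinical success of 99% for pulpotomy and 88% for pulpectomy.

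Reference 31 has no figure anywhere in the article. The Discussion says only that the pulpectomy filling material is among those with the highest reported success. The Abstract and Primary outcomes sections define clinical success and radiographic success separately, and both are assessed at 6, 12 and 24 months.

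**The concern.** One rate, 95%, stands for two primary outcomes, two treatments and three visits, and the article does not say which of these it describes. It is higher than the only radiographic rate quoted and higher than the only pulpectomy rate quoted. Both of those come from shorter follow-up than this trial's 24 months.

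Near 95% the variance changes quickly: p(1−p) is 0.0475 at 95% and 0.09 at 90%, almost double. If success is nearer 90%, a pulpotomy that is truly as good as pulpectomy could easily end with an inconclusive confidence interval. Readers who believe the trial had 80% power might then take that result as evidence against pulpotomy.

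The 78% has the same weakness. It is 95 − 17 and holds only if pulpectomy achieves 95%.

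**Working it through.** **Inputs.** The margin of 0.17, 95% in each arm, 80% power, two-sided alpha of 0.05 and 42 in total (21 per arm) come from Target sample size. The alternative rates of 90%, 93%, 99% (pulpotomy) and 88% (pulpectomy) come from Background/rationale. Where no rate is reported for an arm, the value used is an assumption, marked in the table.

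**Formulas** (normal approximation, unpooled variance; pt = pulpotomy, pc = pulpectomy):

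- n per arm = (z_alpha + z_power)² × [pt(1−pt) + pc(1−pc)] / (0.17 − (pc − pt))²
- power = Φ( (0.17 − (pc − pt)) / SE − z_alpha ), with SE = √([pt(1−pt) + pc(1−pc)] / n)

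**Reproducing the plan's 42.** With 95% in both arms the variance sum is 0.095, and 0.17² = 0.0289.

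- One-sided 0.05: 6.183 × 0.095 / 0.0289 = 20.3, so 21 per arm and 42 in total. This matches.
- Two-sided 0.05 as stated (z = 1.96): 7.849 × 0.095 / 0.0289 = 25.8, so 26 per arm and 52 in total. This does not match.

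The 42 therefore rests on a one-sided 5% test. Both alphas are shown below so that this discrepancy stays separate from the effect of the rates.

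**Power at 21 evaluable per arm**

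| Pulpotomy v pulpectomy | Where the rates come from | One-sided 0.05 | Two-sided 0.05 |
|---|---|---|---|
| 95 v 95 | the plan's assumption | 81% | 71.5% |
| 90 v 90 | reference 29 radiographic; pulpectomy assumed equal | 58% | 45% |
| 90 v 95 | reference 29 radiographic; pulpectomy as the plan assumes | 44% | 32% |
| 93 v 95 | reference 29 clinical; pulpectomy as the plan assumes | 66% | 54% |
| 93 v 93 | reference 29 clinical; pulpectomy assumed equal | 70% | 58% |
| 93 v 88 | clinical rates from references 29 and 30 | 79% | 68% |
| 95 v 88 | pulpotomy as the plan assumes; reference 30 pulpectomy | 88% | 80% |
| 99 v 88 | reference 30, both arms | 98% | 97% |

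Worked example, 90 v 90: SE = √(0.18/21) = 0.0926 and 0.17/0.0926 = 1.836. Then Φ(1.836 − 1.645) = 58% and Φ(1.836 − 1.96) = 45%.

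**If all 50 teeth are evaluable (25 per arm):** 95 v 95 gives 87% and 79%; 90 v 90 gives 64% and 52%.

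**Total N for 80% power at 90 v 90:** 78 at one-sided 0.05 (39 per arm) or 98 at two-sided 0.05 (49 per arm), before attrition.

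**Check on the approximation.** Exact enumeration of the unpooled Wald limit at 21 per arm gives 58% and 48% for 90 v 90, and 77% and 73% for 95 v 95. A Newcombe interval gives less: 55% and 38%, and 65% and 46%.

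**The 78%.** A fixed margin of 17 points accepts 95 − 17 = 78% only if pulpectomy success is 95%. At 88% it accepts 88 − 17 = 71%.

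**The case against.** A reader might infer more: that the article's own sources contradict 95%, and that power is overstated for that reason alone. The documents do not support this, on five grounds.

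- **Range.** The quoted pulpotomy rates run from 90% to 99%, and 95% lies inside that range.
- **Unseen source.** Reference 31 is one of the three sources named and may supply the pulpectomy rate. Without its figure, 95% in that arm cannot be called unsupported.
- **Direction.** In a non-inferiority comparison a lower control rate with pulpotomy unchanged helps. Moving from 95 v 95 to 95 v 88 raises power from 81% to 88% at one-sided 0.05, and from 71.5% to 80% at two-sided 0.05. The 88% is not in itself a reason to expect less power.
- **Mixed endpoints.** Setting 90% for pulpotomy against 88% for pulpectomy joins a radiographic rate from one study to a clinical rate from another. Capping overall success at 90% presumes a composite, whereas the article defines the two outcomes separately and uses the word overall without defining it.
- **Alpha.** Part of the shortfall belongs to the alpha discrepancy: at the stated alpha, 95 v 95 already gives only 71.5%.

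All five stand. They remove the general claim and leave a conditional one. Reference 31 does not close the gap either: if it puts pulpectomy at 95% while pulpotomy is at reference 29's 90% or 93%, power is lower still, at 44% or 66% at one-sided 0.05.

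The 78% is also correct arithmetic under the stated assumption. The complaint is only that it is worded as unconditional.

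**Conclusion.** The point holds in conditional form. The article does not refute 95%, but it does not say what the 95% refers to, and one power figure cannot serve both primary outcomes.

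Two statements are firm. At the stated two-sided 0.05, 42 evaluable teeth give 71.5% power even if 95% is right in both arms. For radiographic success at the only radiographic rate reported, assumed equal in both arms, power is 58% at the alpha behind 42 and 45% at the stated alpha.

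More generally, every pair tried with pulpotomy at reference 29's 90% or 93% and pulpectomy between 88% and 95% falls below 80% at 21 per arm, under either alpha. The closest is 93 v 88, at 79%. Power reaches 80% at the stated alpha for 95 v 88 and 99 v 88.

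These figures rest on the normal approximation, 21 evaluable teeth per arm, and 12- to 18-month rates carried to 24 months. The pulpectomy radiographic rate is an assumption, because the article gives none.

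**What to change.** Keep the sample size and restate what it delivers:

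1. Say which endpoint (clinical, radiographic, or a defined combination) and which visit the 95% refers to, and which source supplies it for each arm.
2. Replace the single 80% claim with a short table of power at the stated alpha over a range of pulpotomy and pulpectomy rates, including 90% for radiographic success. No single base case need be imposed.
3. Reword the 78% as the control rate minus 17 points, which is 78% only if pulpectomy success is 95%.

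The cost is a few lines of text and a less favourable stated power. Recruitment and treatment do not change.

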## Methods

### Trial design

This clinical study is a parallel, two-armed, open label, non-inferiority randomised controlled trial with a 1:1 allocation ratio between the experimental intervention arm (pulpotomy) and the active comparator arm (pulpectomy).

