### Statistical methods

All analyses will use the ‘intention to treat’ principle. Baseline demographic and clinical data will be summarised for each treatment group. Binary logistic regression models will be applied to analyse all outcome measures stated in the protocol adjusting for covariates thought to be of prognostic importance. Appropriate parametric or non-parametric tests will be used to determine any significant relationship between treatment outcomes and variables in the study (age, gender, tooth/caries type, and pre-operative furcal rarefaction/pain intensity). For all statistical tests, we will use 2-sided *p*-values with α ≤ 0.05 and the treatment effect estimates will be presented with 95% confidence intervals. Up-to-date versions of SPSS (Chicago, IL, USA) will be used to conduct the statistical analysis.

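### The 78% pulpotomy success rate described as non-inferior is the boundary of the inferiority null, and the article gives no rule that sets a confidence limit against the 17-point margin

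*Protocol article*

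**What the plan says.** All the design figures are in the protocol article under Target sample size. The assumptions are given as "a 95% success rate was assumed for both treatment interventions along with a 17% non-inferiority margin", followed directly by the sentence at issue: "Even an overall success rate of 78% for the experimental pulpotomy intervention would be considered non-inferior to the standard pulpectomy intervention". It does not say whether 78% is a true or an observed rate.

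The same paragraph gives the error rates ("To obtain a power of 80% (β = 0.20) and a 2-sided α equal to 0.05"), the evaluable number ("approximately 42 patients for both groups will be needed") and the recruitment target ("the targeted sample size will be 50 vital primary molar teeth diagnosed with irreversible pulpitis, distributed equally between the two trial treatment arms"). That is 21 evaluable and 25 randomised teeth per arm.

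The Statistical methods section says that "the treatment effect estimates will be presented with 95% confidence intervals" but does not set any limit against the 17 points. The Hypothesis section does not supply a rule either: it labels non-inferiority itself as the null hypothesis.

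**The concern.** A non-inferiority margin is the smallest true deficit that would be unacceptable, and the trial succeeds when the data exclude it. The sentence works the other way: it takes the assumed control rate, subtracts the margin, and calls the result non-inferior.

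Neither reading of 78% rescues it:

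- **As a true rate**, 78% against 95% is a deficit of exactly 17 points. That is the edge of the null, where a sound test should succeed only at its type I error rate.
- **As an observed rate**, it leaves no room for sampling error, which is large with 21 to 25 teeth per arm.

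The article offers the trial as possible support for a more conservative alternative to the standard treatment. This sentence is its only statement of what result would count as non-inferior. A result near 78% could therefore be reported as a success by citing the protocol, although the data would be compatible with a much larger deficit.

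**Working it through.** **Inputs** (Target sample size; 1:1 allocation from Trial design): success 95% in both arms, margin 17 points, power 80%, α 0.05, 21 evaluable or 25 randomised teeth per arm. The article names no interval method, so Wald, Newcombe (Wilson-based) and score limits are compared.

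**1. The plan's own figures.**

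- Margin: 95 − 17 = 78, so the arithmetic is right.
- Sample size per arm: n = (z₁₋α + z₀.₈₀)² × (0.95×0.05 + 0.95×0.05) / 0.17².
- One-sided 5%: 20.3, rounded up to 21 per arm, 42 in total. This matches the plan.
- One-sided 2.5%, the level of a two-sided 0.05 test: 25.8, rounded up to 26 per arm, 52 in total. This does not match.

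Because the label and the number point to different levels, both 95% and 90% intervals are considered below.

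**2. Lower limit if 78% against 95% is observed.** Wald 95% at 25 per arm:

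SE = √[(0.78×0.22 + 0.95×0.05)/25] = √(0.2191/25) = 0.0936

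Lower limit = −0.17 − 1.96×0.0936 = −0.353

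The Newcombe limit is −0.367. At 21 per arm the two are −0.370 and −0.386.

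**3. The same with whole teeth, 95% limits in percentage points.**

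| Pulpotomy | Pulpectomy | Newcombe | Wald |
|---|---|---|---|
| 19/25 (76%) | 24/25 | −39.7 | −38.4 |
| 20/25 (80%) | 24/25 | −35.4 | −33.5 |
| 16/21 (76%) | 20/21 | −40.7 | −39.4 |
| 17/21 (81%) | 20/21 | −35.6 | −33.4 |

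First row by Newcombe: the Wilson lower limit for 19/25 is 0.566 and the Wilson upper limit for 24/25 is 0.993, so the limit is −0.20 − √[(0.76 − 0.566)² + (0.993 − 0.96)²] = −0.397. With 90% intervals the four rows run from about −30 to −37. Every version is far below −17.

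**4. Observed pulpotomy rate needed when pulpectomy is observed at 95%.** Solve for the rate at which the lower limit equals −17 points. Ranges run from Wald to score, with Newcombe in between.

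| Teeth per arm | Interval | Rate needed | Points above 78% |
|---|---|---|---|
| 25 | 95% | 91.8% to 94.8% | 13.8 to 16.8 |
| 25 | 90% | 90.2% to 92.2% | 12.2 to 14.2 |
| 21 | 95% | 92.6% to 96.2% | 14.6 to 18.2 |
| 21 | 90% | 90.9% to 93.5% | 12.9 to 15.5 |

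In whole teeth at 25 per arm against 24/25, a 95% interval requires 24/25. With 23/25 the limit is −21.3 (Newcombe) or −17.1 (Wald), and both fail.

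**5. Chance of passing when the truth is 78% against 95%** (full enumeration of two independent binomials).

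| Rule | 21 per arm | 25 per arm |
|---|---|---|
| Observed difference no worse than −17 points | 50% | 55% |
| 95% lower limit above −17, Newcombe | 2.3% | 2.2% |
| 95% lower limit above −17, Wald | 4.6% | 3.7% |
| 90% lower limit above −17, Newcombe | 5.6% | 4.8% |
| 90% lower limit above −17, Wald | 6.7% | 7.9% |

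**The case against.** The strongest defence is that the sentence is not a decision rule. It sits in the sample-size paragraph, straight after the margin, and can be read as a gloss on it: a true rate down to about 78% is the loss the investigators would tolerate. It does not use words such as observed or declared. The same paragraph plans with an α and a power, which have no place in a point-estimate rule, and the Statistical methods section promises 95% confidence intervals. An analysis plan that is not shown may give the exact rule and interval method, so their absence from a condensed article is not in itself a fault.

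Much of this stands. The documents do not show that any planned analysis will use 78% as a cut-off, so the false-positive rate of about one half is what would follow if the sentence were applied literally. It is not a forecast.

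A reader might also infer that 78% is a miscalculated threshold, wrong by a fixed amount such as 16 points. The documents do not support that. The subtraction is correct. The comparison sets a margin on the true rate against a cut-off on the observed rate, and that cut-off moves with interval method, confidence level, evaluable number and observed control rate. About 16 to 17 points is only the Newcombe or score result for a 95% interval at 25 per arm.

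The defence does not save the sentence itself. Even as a gloss on the margin, it places the boundary on the acceptable side, when the boundary is what must be excluded. This is a wrong statement in the published text, not a detail left for later.

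**Conclusion.** The point holds as a wrong statement of what counts as non-inferior. On the plan's own assumptions, 78% is the boundary of the null. An observed 78% against about 95% would fail clearly under every interval examined, and about 90% to 96% would have to be observed instead.

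The assumptions are an observed pulpectomy rate close to 95%, 21 to 25 evaluable teeth per arm, and a Wald, Newcombe or score interval at the 90% or 95% level. The required rate shifts with the control result, so the gap of 12 to 18 points is a range under those conditions. The conclusion about a true rate of 78% needs only the stated 95% and the 17-point margin.

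**What to change.** Delete the 78% sentence, or reword it so that 78% is the true pulpotomy rate at the boundary of the null when pulpectomy succeeds in 95%. Then add a rule such as:

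*Pulpotomy will be declared non-inferior only if the lower limit of the two-sided 95% confidence interval for the difference in success (pulpotomy minus pulpectomy) lies above −17 percentage points.*

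Name the interval method with it, since Wald and Newcombe can disagree at this size.

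The cost is a sentence or two in the protocol and the registry record, with no new data. The Trial registration and protocol section and the Dissemination section already provide for amendments. One consequence should be faced at the same time: the 42 teeth reproduce only at one-sided 5%. Under the two-sided 95% rule, which matches the stated α, the normal approximation gives about 71% power with 42 evaluable teeth and about 79% with 50. The sample-size paragraph should be made to agree with whichever level the rule uses.

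### The stated 80% power rests on a large-sample formula at about one expected failure per arm; exact power with 42 evaluable teeth is about 45% (95% interval) or 61% (90% interval) under a score-type rule

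*Protocol article*

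**What the plan says.** The Target sample size section of the protocol article takes its number from an online calculator: "Sample size determination for this binary outcome non-inferiority randomised trial was calculated using a computer-generated system available online". The inputs are printed: "a 95% success rate was assumed for both treatment interventions along with a 17% non-inferiority margin". The margin is an absolute difference, because 95% less 17 points is the 78% in the next sentence: "Even an overall success rate of 78% for the experimental pulpotomy intervention would be considered non-inferior to the standard pulpectomy intervention". The result follows: "To obtain a power of 80% (β = 0.20) and a 2-sided α equal to 0.05, approximately 42 patients for both groups will be needed". Forty-two is the evaluable number, since it is then raised for attrition: "the targeted sample size will be 50 vital primary molar teeth diagnosed with irreversible pulpitis, distributed equally between the two trial treatment arms". The Trial design section gives 1:1 allocation, so 42 means 21 per arm and 50 means 25 per arm.

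The Statistical methods section sets the level for the analysis: "we will use 2-sided *p*-values with α ≤ 0.05 and the treatment effect estimates will be presented with 95% confidence intervals". It plans covariate-adjusted logistic regression and does not name an interval for the difference in success proportions.

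**The concern.** At 95% success, 21 teeth yield 21 × 0.05 = 1.05 expected failures, and an arm has no failure at all with probability 0.95^21 = 34%. The outcome is then close to a count of 0, 1 or 2 failures per arm, and a normal approximation to the difference in proportions cannot be trusted to give the power of a test. The printed 80% should therefore be checked by exact enumeration.

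Two things are at stake. If a rule that roughly holds its error rate is used, the trial is much more likely than stated to miss non-inferiority when the treatments are equal, and a reader told that power was 80% may take the miss as evidence against pulpotomy. If the rule that matches the formula is used, a pulpotomy that is 17 points worse is accepted more often than the stated alpha allows.

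**Working it through.** **Inputs.** From Target sample size: success 0.95 in each arm, margin 0.17, power 0.80, two-sided alpha 0.05, 42 evaluable (21 per arm), target 50 (25 per arm). From Statistical methods: 95% intervals. For non-inferiority, a 95% interval is a one-sided 2.5% test and a 90% interval a one-sided 5% test.

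**Reproducing 42.** Unpooled normal formula: n per arm = (z_α + z_β)² × 2 × 0.95 × 0.05 / 0.17².
- One-sided 5%: (1.645 + 0.842)² × 0.095 / 0.0289 = 20.3, so 21 per arm and 42 in total. This matches.
- One-sided 2.5%: (1.960 + 0.842)² × 0.095 / 0.0289 = 25.8, so 26 per arm and 52 in total. This does not match.

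Formula power at 21 per arm is Φ(0.17 / √(0.095/21) − z) = Φ(2.53 − z): 81.1% at z = 1.645 and 71.5% at z = 1.960.

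**Exact power at 21 per arm.** For each number of pulpectomy failures, find the largest number of pulpotomy failures for which the interval's lower limit stays above −0.17, then sum the binomial probabilities. With failure probability 0.05, P(0), P(1), P(2), P(3), P(4) = 0.3406, 0.3764, 0.1981, 0.0660, 0.0156. The cumulative values to 3 are 0.3406, 0.7170, 0.9151, 0.9811.

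| Interval | Pulpotomy failures allowed at 0, 1, 2, 3, 4 pulpectomy failures | Exact power at 95% v 95% | Error at 78% v 95% |
|---|---|---|---|
| Farrington-Manning 95% | 0, 0, 1, 1, 2 | 45.1% | 1.7% |
| Newcombe 95% | 0, 0, 1, 2, 2 | 46.4% | 2.3% |
| Wald 95% | 1, 1, 1, 2, 2 | 73.4% | 4.6% |
| Farrington-Manning 90% | 0, 1, 1, 2, 3 | 60.7% | 3.8% |
| Newcombe 90% | 0, 1, 2, 2, 3 | 64.6% | 5.6% |
| Wald 90% | 1, 1, 2, 2, 3 | 77.4% | 6.7% |

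The first row in full: 0.3406 × 0.3406 + 0.3764 × 0.3406 + 0.1981 × 0.7170 + 0.0660 × 0.7170 + 0.0156 × 0.9151 = 0.448. Five or more pulpectomy failures add about 0.003, which gives 0.451.

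**Where Wald gains.** Against Newcombe at 95%, Wald also accepts two common outcomes. One pulpotomy failure against none has probability 0.3764 × 0.3406 = 12.8%. One against one has probability 0.3764² = 14.2%. Together these make up the 27-point gap.

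**Wald error at its worst.** If pulpectomy never fails, pulpotomy at the margin succeeds with probability 0.83, and Wald accepts up to one failure: 0.83^21 + 21 × 0.17 × 0.83^20 = 10.6%. At 97% pulpectomy success the error of the 95% Wald interval is 6.1%.

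**All 50 evaluable (25 per arm).** Farrington-Manning and Newcombe both give 57.4% with a 95% interval and 73.7% with a 90% interval. The 95% Wald interval gives 72.8%, with 3.7% error at 78% v 95%.

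**26 per arm, the formula's answer for two-sided 0.05.** The 95% score-type intervals give 56.6%. The 95% Wald interval gives 80.3%, with 4.8% error against 2.5%.

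**The case against.** The number comes from a standard, cited calculator, and 42 follows from its inputs once the level is read as one-sided 5%. The 45-65% range depends on the choice of interval, and the article names none. An article may leave that choice to the analysis plan, so its absence is not itself a fault. All of this stands. The formula is also inferred from the exact match at 42, because it is not printed.

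A reader might go further than the documents allow in four ways.
- That no test could come near 80%. This is not so. Wald has 73-77% exact power at 42 and 80.3% at 52, and Agresti-Caffo at 95% has 60.6% at 42, with 3.5% error at 78% v 95%. The 80% is approached only by rules that exceed the nominal error.
- That the trial plans a Wald interval. Statistical methods does not say so; Wald matters here only because it corresponds to the formula.
- That Wald gains power solely because its variance collapses when an arm has no failures. More than half of the gap at 95% comes from the one-against-one outcome, where neither arm is at zero.
- That a 10.6% error applies at the design assumption. It arises only as pulpectomy success approaches 100%.

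The score-type methods are not perfect either. Newcombe's 90% interval has 5.6% error against 5% at 78% v 95%, so the 61% from Farrington-Manning is the safer figure for a 90% rule.

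What remains is that the power is a printed number and does not hold for its own inputs with 42 evaluable teeth under any interval tabulated above, at either level.

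**Conclusion.** The stated 80% power is wrong as written. With 42 evaluable teeth, exact power is about 45-46% for a 95% score-type interval and about 61% (65% with Newcombe) for a 90% one; with all 50 it is 57% and 74%. Under the 95% rule, equal treatments at 95% success would fail to show non-inferiority about 54-55% of the time. Wald falls short by less, at 73% or 77% with 42, and its error at 78% v 95% is 4.6% against 2.5%, or 6.7% against 5%.

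This is separate from the one- or two-sided wording of alpha: settling that alone would leave the power figure wrong at 42. The conclusion assumes 95% success in both arms, an absolute 17-point margin, 42 as the evaluable number, and a decision based on the unadjusted difference in proportions. The power of a rule based on the planned logistic regression was not calculated.

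It does not follow that the trial must be enlarged. For orientation, 80% exact power by a score-type rule would need about 27-30 evaluable teeth per arm (54-60 in total) at one-sided 5%, or 39 per arm (78 in total) at one-sided 2.5%. A trial of the planned size can still be reported honestly if its power is stated correctly.

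**What to change.** In Statistical methods, name a score-type interval for the risk difference (Farrington-Manning/Miettinen-Nurminen, or Newcombe) as the non-inferiority rule, with the lower limit compared with −17 points. The 95% interval already planned is preferable. In Target sample size, replace the 80% with the exact binomial power of that rule: about 45% with 42 evaluable and 57% with 50 for a 95% interval, or about 61% and 74% if a 90% interval is intended. Add a sentence that failing to show non-inferiority at this size is not evidence that pulpotomy is inferior.

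The cost is rewording two paragraphs and a less favourable stated power. The interval can be computed from the 2×2 table, and enrolment is unchanged.

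### The total of 42 patients gives 80% power only with a one-sided 5% test; at the stated two-sided 0.05, power is about 71% with 42 evaluable and about 79% if all 50 are retained

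*Protocol article*

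**What the plan says.** The article describes a "non-inferiority randomised controlled trial with a 1:1 allocation ratio" (Trial design). The sample size inputs are all in the Target sample size section:

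- Rates and margin: "a 95% success rate was assumed for both treatment interventions along with a 17% non-inferiority margin".
- The margin is an absolute difference, since the text adds: "Even an overall success rate of 78% for the experimental pulpotomy intervention would be considered non-inferior to the standard pulpectomy intervention" (95% − 17% = 78%).
- Power: "To obtain a power of 80% (β = 0.20").
- Alpha and result: "a 2-sided α equal to 0.05, approximately 42 patients for both groups will be needed".

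The total is then raised to 50 teeth, split equally between the arms, to allow for loss to follow-up and other attrition. No attrition rate is given, but going from 42 to 50 implies 1 − 42/50 = 16%.

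For the analysis, the Statistical methods section says: "we will use 2-sided *p*-values with α ≤ 0.05 and the treatment effect estimates will be presented with 95% confidence intervals". Neither section mentions a one-sided 5% test or a 90% interval.

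**The concern.** A non-inferiority claim is decided in one direction. Two-sided alpha 0.05, or a 95% interval compared with the margin, puts 2.5% in that direction. Both the sample size section and the analysis section point to that level. The number 42 points to 5%.

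Two things follow. First, the trial states a power that it does not have at its stated alpha, so a failure to show non-inferiority could be misread as evidence against pulpotomy when it may only reflect limited power. Second, the decision threshold is left open. An analyst could use a 95% interval because the text says so, or argue afterwards for a 90% interval because the sample size was built on one. With about 21 to 25 teeth per arm, that choice can change the conclusion.

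**Working it through.** **Inputs (Target sample size section):** success p = 0.95 in both arms, so the true difference is 0; margin d = 0.17; power 80% (z = 0.8416); 1:1 allocation.

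**Formula (unpooled normal approximation):**
n per arm = (z_alpha + z_beta)² × 2p(1 − p) / d²
where 2p(1 − p) = 2 × 0.95 × 0.05 = 0.095 and d² = 0.0289.

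**Step 1. Reproduce the plan's figure.**
One-sided 0.05: (1.6449 + 0.8416)² = 6.183.
6.183 × 0.095 / 0.0289 = 20.3, rounded up to 21 per arm, **42 in total**. This matches.

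**Step 2. Use the stated alpha.**
Two-sided 0.05, i.e. 0.025 in the non-inferiority direction: (1.9600 + 0.8416)² = 7.849.
7.849 × 0.095 / 0.0289 = 25.8, rounded up to 26 per arm, **52 in total**.

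**Step 3. Could another method give 42 at the stated alpha?** At one-sided 0.025:

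| Variant | Total |
|---|---|
| Continuity correction | 74 |
| Null-variance forms | 96 to 102 |
| 90% power | 70 |
| Superiority test, 95% vs 78% | 126 |

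None gives 42. Nor can 42 be a per-arm figure, because the inflated total of 50 is divided between the two arms.

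**Step 4. Power at the stated alpha.**
Power = Φ(d / √(0.095/n) − 1.96)

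| Evaluable teeth | n per arm | d / SE | Power, two-sided 0.05 | Power, one-sided 0.05 |
|---|---|---|---|---|
| 42 | 21 | 2.528 | 71.5% | 81.1% |
| 50 | 25 | 2.758 | 78.8% | 86.7% |
| 52 | 26 | 2.812 | 80.3% | 87.9% |

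**Step 5. Sensitivity cases, separate from the error.**

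- *Success rate of 90% in both arms (an assumed scenario).* 2p(1 − p) = 0.18. Formula power at two-sided 0.05 is 45% with 42 and 52% with 50. The total needed is 98 (7.849 × 0.18 / 0.0289 = 48.9, so 49 per arm).
- *Exact power by enumerating binomial outcomes at 95% success, 95% interval (interval type assumed).* Newcombe: 46% with 42 and 57% with 50. Wald: about 73% at both sizes.

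**The case against.** The strongest defence concerns size. The text says the number is approximate, and with full retention the 50 teeth fall only two short of 52, costing 80 − 78.8 = 1.2 points of power. That is fair for the 50-tooth case. It does not cover the 42-tooth case: the extra eight teeth are there to absorb losses over two years, so 42 evaluable is what the plan sizes for. There the gap is ten teeth, or about 8.5 points of power.

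Three stronger readings are tempting and are not supported.

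1. **That true power is only 46% to 57%.** A reader might infer this from the Newcombe results, but the article names no interval method for the difference, and the result depends on it. Most of that gap comes from the normal approximation with few failures, not from the alpha mismatch: even at 26 per arm, where the formula gives 80.3%, exact Newcombe power is about 57%.

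2. **That the 95% success rate is shown to be too high.** The Background/rationale section reports a cohort that "reported 93% clinical success and 90% radiographic success after one year of treatment". It also cites a retrospective study with 88% clinical success for pulpectomy, but that study found 99% for pulpotomy. Taken as a pair, 99% against 88% gives formula power of about 97% with 42 and 98% with 50, so the 88% cannot be used alone as evidence of lower power. The sample size section also relies on a third cited source whose figure the article does not give. The 90% case is therefore a scenario only.

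3. **That the article already fixes a 95% interval as the decision rule.** The Statistical methods section says only that estimates are presented with such intervals. It is consistent with the two-sided 0.05 in the sample size section, but no rule against the margin is stated.

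**Conclusion.** The sample size statement is wrong as written. On its own inputs, 42 in total belongs to a one-sided 5% test. The two-sided 0.05 that the article states requires 52 evaluable teeth, more than the attrition-inflated target of 50. Power at the stated alpha is about 71% with 42 evaluable and about 79% with all 50, against a stated 80%. The material shortfall is at 42; at 50 it is marginal.

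These figures rest on the article's own 95% success rates, its 17-point absolute margin and the unpooled normal approximation, which reproduces 42 exactly at one-sided 5%. The conclusion does not depend on doubting the 95% rate or on any particular interval method.

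**What to change.** Reconcile alpha and sample size in the Target sample size and Statistical methods sections before outcome data are seen, by one of two routes.

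(a) Keep two-sided 0.05. State that non-inferiority is judged by comparing the 95% confidence interval for the difference with the 17-point margin, and restate the power as about 71% with 42 evaluable teeth and about 79% with 50 (normal approximation).

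(b) Declare a one-sided 5% test with a 90% confidence interval in both sections, and acknowledge that this raises the false non-inferiority rate from 2.5% to 5%. The figure of 42 then stands.

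Both routes change text only and need no extra patients. Route (a) costs a less favourable power statement; route (b) costs a weaker standard of evidence. If the sponsor wants 80% power at two-sided 0.05, that takes 52 evaluable teeth, or about 62 randomised at the implied 16% loss (52 / 0.84 = 61.9).

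The 90% success scenario and the exact-power results may be added if labelled as sensitivity cases, with the interval method named.
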